### Quantitative methodology: Primary outcome

The primary outcome of the quantitative study component is days alive and out of hospital (DAOH) at 30 days after surgery. This patient-centred outcome measure has been clinically validated internationally and is related to clinically relevant patient characteristics, surgical complexity, in-hospital complications, and long-term outcomes [24–26]. We will also assess DAOH at 180 and 365 postoperative days to provide information on longer term mortality outcomes [27].

We will use similar methodology to construct DAOH as detailed elsewhere [27,28]. Specifically, to calculate DAOH of a defined period, we will subtract the total post-operative duration of initial and any next subsequent hospital stays from the total period length to obtain the numbers of days spent out of hospital. The time spent in a non-hospital care facility will not be accounted for in our analyses [27]. DAOH will be defined as 0 days if a patient died within the defined period. A longer DAOH will be indicative of more favourable outcome. For each DAOH at 30, 180 and 365 variable respectively, there will be a ceiling 30/180/365. DAOH data will be calculated based on event date of corresponding operation procedure ICD-10 code, length of stay data related to each hospital admission and subsequent re-admission, discharge date and discharge destination from HES APC dataset and death date from HES-ONS linked mortality dataset.

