### Quantitative methodology: Effectiveness statistical analysis

The study population is defined to align with the qualitative component of the study. That is, all adults undergoing colorectal cancer surgery, repair of abdominal aortic aneurism or knee replacement at an NHS hospital in England between Jan 1^st^ 2018 and April 1^st^ 2026 in HES APC dataset.

In the absence of randomisation, quasi-experimental research designs are increasingly used for evaluating population health interventions [32,33]. In this analysis, we will use an interrupted times series research design: this method has been widely used to evaluate health interventions with time series data [34].

HES provides a long time series dataset, and, without a control group, a single interrupted time series analysis is the most suitable design to evaluate the programme [35]. We will conduct segmented regression analysis on monthly DAOH measures, postoperative length of stay, rate of emergency re-admission in 30 days,days spent in critical care and also relevant costs [36].

Based on date of surgery, in this analysis we will model monthly data at different time periods between Jan 1st 2018 to Jan 1st 2026, with Jan 2018 to end of Feb 2023 data as baseline period. Intervention period is March 2023 to end of March 2024. Post-intervention period is April 2024 to April 2026.

Specifically, we will model the following:

$$Y_{t}=\;\beta_{\text{0}}+\beta_{\text{1}}T+\beta_{\text{2}}X_{\text{1}t}+\beta_{\text{3}}{(T-T_{i})X}_{\text{1}t}\;+\beta_{\text{4}}X_{\text{2}t}+\beta_{\text{5}}{(T-T_{d})X}_{\text{2}t}\;+\;\varepsilon_{t}$$

Where Yt is the outcome at time t, T represents the time since the start of the study, X_1t_ is a dummy (0/1) variable indicating the intervention period [1] or otherwise 0, X_2t_ is a dummy variable representing the post-intervention period, Ti represents the time point when the intervention starts (X_1t_=1 for T ≥ Ti). Td represents the time point when the post-intervention period starts (X_2t_=1 for T ≥ Td). [37]

$\beta_{\text{0}}$ represents the baseline level of Y at T=0

$\beta_{\text{1}}$ represents underlying pre-intervention trend

$\beta_{\text{2}}$ represents the intercept change immediately following the intervention

$\beta_{\text{3}}$ represents the change in the slope of the trend following the intervention

$\beta_{\text{4}}$ represents the intercept change immediately post the intervention

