$\beta_{\text{5}}$ represents the change in the slope of the trend post the intervention

Details of this methodology are available elsewhere [37].

In our analysis, by stratification, we will examine variations in time trend patterns in geographic location and patients characteristics including age groups, gender, ethnicity and deprivation measured using Index of Multiple Deprivation quantiles. We will use region of residence and local integrated care board in HES data to indicate geographical locations. Age will be grouped as 18–44, 45–65, 66–79, and 80 plus [38]. Ethnicity will be grouped based on ONS 2021 census ethnic categories, including White, Asian and Asian British, Black and Black British, Mixed or multiple ethnic groups, and Other ethnic group. In addition, we will explore variations in NHS hospital sites.

We will also check for seasonality impacts through sensitivity analyses such as using time stratified model, periodic functions or flexible spline functions that are detailed elsewhere [39]. The timing of rollout of the intervention was likely to be different across hospitals, therefore, we will conduct a sensitivity analysis with different definitions of the intervention period (i.e., early implementation period- 1^st^ March to 31^st^ Aug 2023 vs late implementation period – 1^st^ Sep 2023–31^st^ March 2024). Given the dramatic impact of Covid on health services, we will also assess the impact of a shorter baseline period of between Jan 2018 to Feb 2020. In addition, concurrent national programmes that target similar outcomes, such as Getting it Right First Time (GIRFT) [40], could confound our results. We will conduct sensitivity analyses that will stratify by different time periods to adjust for relevant national programmes if there are well-documented dates of implementation and can be distinctly modelled within our time series. We will conduct complete case analyses. Stata 17 (StataCorp) and R 4.2.2 (R Core Team, 2022) will be used to conduct the analysis.

Finally, to examine short-term cancellation, we will conduct descriptive data analysis and describe short-term cancellation data across different time periods and geographical regions.

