The quantitative effectiveness evaluation has several important limitations. First, the study lacks a randomised control group because the early screening programme was implemented nationally across England in all specialties and we only have data for hospitals in England. Without a control group, this makes a single interrupted time series analysis the most suitable approach. Second, the analysis cannot definitively link the intervention to individual patients, relying instead on the timing of the programme’s implementation. This is due to the level of uncertainties around exact timing of the programme’s rollout and differences in pre-existing established early screening and optimisation services across different hospitals in the country. To deal with this, we will conduct several sensitivity analyses using different start dates for the intervention period to account for both early and late implementation and also stratify our analyses by regions or hospitals using results from our short-term cancellation data and qualitative study. Third, this design is susceptible to confounding from co-occurring events and policy changes in the same period. To address confounding events such as in the case of COVID, we will be conducting a sensitivity analysis using a shorter pre-COVID baseline period and by using our qualitative findings to provide context for any observed changes. Fourth, unmeasured confounding may also bias our results. Fifth, the analysis relies on routinely collected hospital data, which may have data quality concerns [43]. To address this, we will conduct thorough data cleaning and preparation to ensure our findings are robust.

We acknowledge that programme success is more complex than simple statistical improvements. It is possible that the programme’s success is demonstrated by widening access to surgery for higher-risk patients who would have been previously excluded, which might result in static or even worsened postoperative complication rates and lengths of stay. To account for this, we will also monitor changes in underlying patient characteristics, such as the percentage of patients in the most deprived quintile of the Index of Multiple Deprivation, which is strongly correlated with multimorbidity rates [44].

Table 4 provides a summary outlining the key components of the study.

**Table 4 pone.0335129.t004:** Summary Table outlining key components of the study.

	Qualitative	Quantitative

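### The pre-COVID baseline is cut by date of surgery, so for DAOH180 and DAOH365 its last months still contain COVID follow-up and the check cannot do its stated job for those two outcomes

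*Protocol article*

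**What the plan says.** Four statements in the protocol article bear on this.

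- **Time axis** (Effectiveness statistical analysis): "Based on date of surgery, in this analysis we will model monthly data". All DAOH measures go into the segmented regression, with one linear pre-intervention trend, β1.
- **Outcomes** (Primary outcome): the primary is "days alive and out of hospital (DAOH) at 30 days after surgery". The article adds "We will also assess DAOH at 180 and 365 postoperative days to provide information on longer term mortality outcomes". Later hospital stays are subtracted, and "DAOH will be defined as 0 days if a patient died within the defined period".
- **COVID check** (Effectiveness statistical analysis): "we will also assess the impact of a shorter baseline period of between Jan 2018 to Feb 2020". One cut date is given. Nothing ties it to the length of follow-up or limits the check to DAOH30.
- **Purpose of the check** (Discussion, third limitation): "we will be conducting a sensitivity analysis using a shorter pre-COVID baseline period". The same sentence adds that qualitative findings will give context.

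The intervention period starts in March 2023 and the post-intervention period in April 2024. The article gives no COVID effect size and does not say how March 2020 to February 2023 is handled when the short baseline is used.

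**The concern.** A cut by date of surgery separates pre-COVID from COVID experience only when the outcome is complete soon after surgery. DAOH365 for a patient operated on in mid-2019 depends on deaths and admissions well into 2020. So a baseline that is pre-COVID by surgery date is not pre-COVID by outcome for the two longer windows.

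The form of the contamination matters more than its presence. It is zero through the early baseline, then rises month by month to nearly complete in February 2020. A straight line fitted to those months reads the rise as a trend, and that trend is projected 36 months to the start of the intervention period and 49 months to the start of the post-intervention period.

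DAOH180 and DAOH365 are the outcomes closest to the research question on long-term health. For them, neither agreement nor disagreement between this check and the main analysis could be read as evidence about COVID.

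**Working it through.** The article states no figure for this analysis, so there is none to reproduce. The check uses its dates and definitions.

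**Inputs**
- Short baseline: January 2018 to February 2020, 26 surgery months, indexed t = 0 to 25 (mean 12.5, Sxx = 1462.5).
- Windows: K = 30, 180, 365 days from surgery.
- March 2023 is t = 62; April 2024 is t = 75.
- Assumption: COVID starts on 1 March 2020, the date implied by the February 2020 cut. Range tried: 1 February to 23 March 2020.

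**Step 1. Exposed share by surgery month.** For each surgery day, share = (days of the K-day window on or after 1 March 2020) / K, averaged over the month.

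| Outcome | Months with any exposure | First such month | Share in Feb 2020 |
|---|---|---|---|
| DAOH365 | 12 of 26 | March 2019 | 0.96 |
| DAOH180 | 6 of 26 | September 2019 | 0.92 |
| DAOH30 | 1 of 26 | February 2020 | 0.50 |

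For DAOH365 the 12 shares run 0.04, 0.12, 0.21, 0.29, 0.37, 0.46, 0.54, 0.63, 0.71, 0.79, 0.88, 0.96. With a COVID start of 1 February 2020 the counts are 13, 7 and 2; with 23 March 2020 they are 12, 6 and 1.

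**Step 2. Slope and projection.** Let D be the change in mean DAOH when the whole window lies in COVID, with the effect proportional to overlap and D specific to each outcome. Error in the counterfactual at time t = D × [mean share + slope × (t − 12.5)].

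- DAOH365: mean share 0.230, slope 53.88 / 1462.5 = 0.0368 per month. March 2023: 0.230 + 0.0368 × 49.5 = 2.05D. April 2024: 0.230 + 0.0368 × 62.5 = 2.53D.
- DAOH180: mean share 0.114, slope 32.58 / 1462.5 = 0.0223. March 2023: 1.22D. April 2024: 1.51D.
- DAOH30: mean share 0.019, slope 6.25 / 1462.5 = 0.0043. March 2023: 0.23D. April 2024: 0.29D.

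Over the range of COVID start dates the DAOH365 slope runs from 0.033D to 0.041D per month, and the April 2024 error from 2.29D to 2.84D.

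**Step 3. Which coefficients carry the error.** I fitted the article's model without noise to DAOH365, with no programme effect, no COVID effect by 2023, March 2020 to February 2023 left out, and D = −1 day. The article describes X1 in two ways: as 1 in the intervention period and 0 otherwise, and as 1 at every time from Ti onward.

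| Coding of X1 | β2 | β3 | β4 | β5 |
|---|---|---|---|---|
| 1 in the intervention period only | +2.05 | +0.037 | +2.53 | +0.037 |
| 1 from Ti onward | +2.05 | +0.037 | 0 | 0 |

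All of these are spurious, and D = +1 reverses the signs.

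**Step 4. Cost of a clean cut.** Follow-up ends before 1 March 2020 for surgery to end January 2020 (DAOH30, 25 months), end August 2019 (DAOH180, 20 months) and end February 2019 (DAOH365, 14 months). With independent errors, the SE of the projected counterfactual at April 2024, in residual SDs, is √[1/n + (75 − t̄)²/Sxx]:

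- n = 26: √(1/26 + 62.5²/1462.5) = 1.65
- n = 20: √(1/20 + 65.5²/665) = 2.55
- n = 14: √(1/14 + 68.5²/227.5) = 4.55

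**Step 5. An exposure covariate.** If the covariate is the share of follow-up on or after 1 March 2020 with no end date, it equals 1 in every month from March 2023. Refitting under the Step 3 assumptions removes the false slope but leaves a false level shift of 1.0D in magnitude in β2. If the COVID period has an end date, so that the covariate is 0 in those months, all spurious terms vanish.

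**The case against.** - **The primary result is not at risk.** A reader might infer that the main COVID safeguard fails throughout. It does not: DAOH30 is touched in one month of 26, and 30-day readmission also has a short window. The defect sits in one sensitivity analysis of two further DAOH windows. This stands.
- **It is not the only protection against COVID.** The Discussion also names qualitative context. What can be said is that this is the only quantitative COVID check named.
- **The bias in days is unknown.** It is tempting to quote a false benefit of so many days. The documents give neither the size nor the sign of D: deaths would lower DAOH and fewer admissions would raise it. D = −1 and D = +1 give false effects of about +2.5 and −2.5 days for DAOH365 at April 2024, as illustration only. Part of the multiplier is simply the leverage of a 26-month line carried 49 months, which would magnify any baseline error.
- **β4 need not be biased.** If X1 stays at 1 after March 2024, the error falls on β2 and β3 alone. A claim that the post-intervention coefficients are wrong by 2.5D goes beyond the document.
- **Outcome-specific cuts may be in the analysis plan.** That plan is not shown and is due for revision. But the article does not leave the matter open: it fixes one cut date and labels the period pre-COVID, which is inaccurate for two of the three DAOH outcomes.

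**Conclusion.** The point holds for DAOH180 and DAOH365. The calendar overlap follows from the article's own dates and hardly depends on the exact COVID start. The counterfactual error of about 2.1D and 2.5D (DAOH365) and 1.2D and 1.5D (DAOH180) at March 2023 and April 2024 rests on four assumptions: an effect proportional to overlap, a single D per outcome, no COVID effect by 2023, and March 2020 to February 2023 left out. If D were zero there would be no bias, but the article itself justifies the check by a large COVID impact on services. As written, the check cannot separate COVID from the programme for the two longer-term outcomes. This deserves correction before analysis but does not threaten the primary outcome.

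**What to change.** 1. Define the pre-COVID baseline by end of follow-up: surgery to end January 2020 for DAOH30, end August 2019 for DAOH180 and end February 2019 for DAOH365.
2. State that the February 2020 cut is pre-COVID only for short-window outcomes.
3. For DAOH365, choose one of two routes in advance. Either report the 14-month check as weak, or keep January 2018 to February 2020 and add the monthly share of follow-up days inside a COVID period with a stated start and end, so that the covariate is 0 in the 2023–26 months. The second route relies on the effect being proportional to overlap.
4. State how X1 is coded after March 2024 and what happens to March 2020 to February 2023 in this check, since both decide where any remaining error falls.

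This needs wording and a few lines of code, and no new data. The price is precision: at April 2024 the counterfactual SE rises from 1.65 residual SDs to 2.55 for DAOH180 and 4.55 for DAOH365 under the clean cut. The covariate route also widens the intervals, because the share is strongly related to time.

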### Integrated approach

The study will take a convergent design by carrying out a qualitative implementation evaluation alongside a quantitative effectiveness evaluation [41]. While the qualitative and quantitative analysis will be performed separately, the results will be presented using joint display tables to compare and relate data [41].

To better integrate our mixed-methods approach, we will utilise findings from our qualitative implementation evaluation to inform our quantitative analysis. Our qualitative study will provide rich and contextual understanding of implementation barriers and facilitators. While it is not possible to do this for all hospitals in HES dataset, we will develop a typology of implementation. This will allow us to categorise the measured level and success of implementation of the programme from five study sites and then conduct a quantitative case study analysis to explore the relationship between the measured success/maturity of implementation and patient level outcomes, and will facilitate a more nuanced interpretation of the national findings.

## Discussion

Early screening, triaging, risk assessment and health optimisation in perioperative pathways is an important programme built on evidence that may lead to improvement in patient outcomes and NHS efficiency. This mixed methods study will explore staff and patient experiences and perceptions, as well as assess the impact of the programme on patient centred outcomes using routinely collected hospital data and quasi-experimental research methods.

The implementation evaluation will be carried out across multiple NHS Regions providing preliminary findings as the evaluation is ongoing. This will facilitate real time insights, delivered to stakeholders through formative feedback, allowing us to explore the barriers and facilitators as they happen and at different stages of implementation as some sites will be further developed than others. This process of providing formative feedback will offer the opportunity for stakeholders to further improve implementation strategies through real time adaptation [42]. Another key strength of this research is that we are able to use data from all hospitals in England to evaluate a range of patient level outcomes and cost analysis.

The quantitative effectiveness evaluation has several important limitations. First, the study lacks a randomised control group because the early screening programme was implemented nationally across England in all specialties and we only have data for hospitals in England. Without a control group, this makes a single interrupted time series analysis the most suitable approach. Second, the analysis cannot definitively link the intervention to individual patients, relying instead on the timing of the programme’s implementation. This is due to the level of uncertainties around exact timing of the programme’s rollout and differences in pre-existing established early screening and optimisation services across different hospitals in the country. To deal with this, we will conduct several sensitivity analyses using different start dates for the intervention period to account for both early and late implementation and also stratify our analyses by regions or hospitals using results from our short-term cancellation data and qualitative study. Third, this design is susceptible to confounding from co-occurring events and policy changes in the same period. To address confounding events such as in the case of COVID, we will be conducting a sensitivity analysis using a shorter pre-COVID baseline period and by using our qualitative findings to provide context for any observed changes. Fourth, unmeasured confounding may also bias our results. Fifth, the analysis relies on routinely collected hospital data, which may have data quality concerns [43]. To address this, we will conduct thorough data cleaning and preparation to ensure our findings are robust.

We acknowledge that programme success is more complex than simple statistical improvements. It is possible that the programme’s success is demonstrated by widening access to surgery for higher-risk patients who would have been previously excluded, which might result in static or even worsened postoperative complication rates and lengths of stay. To account for this, we will also monitor changes in underlying patient characteristics, such as the percentage of patients in the most deprived quintile of the Index of Multiple Deprivation, which is strongly correlated with multimorbidity rates [44].

Table 4 provides a summary outlining the key components of the study.

**Table 4 pone.0335129.t004:** Summary Table outlining key components of the study.

	Qualitative	Quantitative
Research questions	Programme design and implementation 1. How was the programme designed, and what factors influenced this? 2. How are different NHS settings implementing the programme and to what extent are the activities implemented? 3. What are the experiences of those implementing and delivering the programme? 4. What are the barriers and facilitators for different NHS sites in implementing the programme? Patient experience 1. What are patient perceptions and experiences of the preoperative optimisation process? 2. To what extent do patients feel informed and supported in shared decision-making regarding their surgical care? 3. Has the implementation of this programme resulted in changes to patient care as anticipated?	Patient Outcomes and Health Impact 1. How does early preoperative screening impact rates of postoperative complications and patient recovery times? 2. What effect does early screening and optimisation have on rates of short-notice surgical cancellations? 3. To what extent does early identification and optimisation of health risks influence long-term health outcomes for patients? Cost implications and Resource Allocation 1. What are the cost implications of early preoperative screening and optimisation on healthcare resources and system efficiency?
Timelines	Months 1–2 – Implementation evaluation; gaining ethical and local research governance permissions. Months 3–13 – Implementation evaluation; recruitment, data collection and analysis will run in parallel. Interim findings disseminated. Should any sites experience delays in implementation, the data collection period will be extended. Month 14 – Implementation evaluation; final write-up and submission of outputs. Participant recruitment for the implementation evaluation has begun.	Months 0–9 – Effectiveness evaluation; submit HES data access application, work to gain access to the linked dataset. While waiting for the data access, we will revise our statistical analysis plan. Months 10–12 – Effectiveness evaluation; data cleaning and exploratory data analysis. Interim findings disseminated via internal reports and presentations. Months 13–18 – Effectiveness evaluation; finalise statistical analysis, write-up and submission of outputs.
Data sources	Qualitative implementation evaluation: • Staff and patient interviews • Non-participant observations • Document review	Quantitative effectiveness evaluation: • Hospital Episodes Statistics (HES)

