In 2023, all NHS hospitals in England were asked to implement a programme of early screening, triaging, risk assessment and health optimisation [11]. This included pre-assessment questionnaires and establishing an expanded perioperative care workforce. The directive was published in the 2023/24 NHS Standard Contract [14] followed by guidance published in May 2023 [11].These teams could consist of, for example, care co-ordinators, nurses and perioperative physicians who carry out assessments of health needs to identify surgical risk factors and inform pre- and post-operative care. The team would identify low-risk patients who do not need to attend face-to-face preoperative assessment and patients who could be treated in elective hubs focused on providing High Volume Low Complexity (HVLC) surgery. These services are intended to facilitate early shared decision making and optimisation of patient health, increasing patients’ suitability and readiness for surgery. A key anticipated benefit of these changes is increased safety through reduced perioperative complications (both in terms of complications from surgery, and the psychological harms associated with last-minute cancellations) [11]. The programme may also increase efficiency, e.g., through reductions in last-minute cancellations, reductions in length of hospital stay, and identifying people who can undergo surgery without requiring an overnight hospital stay [11].

The requirement for an early screening, triaging, risk assessment and health optimisation programme (hereinafter referred to as “the programme”) to be implemented was included in the NHS 2023/24 contract with the stipulation that the programme was to be implemented “no later than 31 March 2024”. This is a national programme, with implementation taking place across multiple NHS hospital organisations, in diverse geographic and socioeconomic contexts and within a variety of surgical pathways. It is likely that implementation progressed variably across different clinical and organisational settings. In addition, some settings or specialties (e.g., bariatric surgery) [15] have more well-established multidisciplinary preoperative pathways which aim to optimise comorbidities and reduce the risk of patients undergoing surgery without critical modifiable health issues having been addressed. In this manuscript we describe the mixed methods approach we will adopt to examine the implementation and impact of the new screening programme.

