### Quantitative methodology: Effectiveness evaluation

### Data sources

For the effectiveness evaluation, we will use a cohort study research design using Hospital Episodes Statistics (HES) data. A bespoke dataset extracted from Hospital Episodes Statistics Admitted Patient Care (HES-APC), Critical Care (HES-CC) and HES linked Office for National Statistics (ONS) mortality data will be used to conduct this analysis.

HES is a high quality national secondary care database that reports all NHS hospital admissions in England. It includes detailed information on hospital activities including admission dates, diagnoses and procedures, duration of stay and patient demographic information [22]. The access to the data is managed by NHS Digital. Relevant data fields used in this research are detailed in S4 File.

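### The programme can change who is operated on, in either direction, but outcomes are counted only in operated patients and the stated remedy is to monitor patient mix, which does not adjust the estimate.

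*Protocol article*

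**What the plan says.** The effectiveness analysis takes "all adults undergoing colorectal cancer surgery, repair of abdominal aortic aneurism or knee replacement at an NHS hospital in England" (Effectiveness statistical analysis section). The primary outcome is "days alive and out of hospital (DAOH) at 30 days after surgery" (Primary outcome section). Length of stay, 30-day emergency readmission, critical-care days and costs are taken from the same operated patients.

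The programme acts earlier in the pathway. The Introduction says: "These services are intended to facilitate early shared decision making and optimisation of patient health, increasing patients’ suitability and readiness for surgery".

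The segmented model contains an intercept, a time trend, and level and slope changes for the intervention and post-intervention periods. It has no term for patient risk. Separately, trends are to be examined in strata of geography, age group, gender, ethnicity and deprivation, and variation between hospital sites explored. Comorbidity is not among the strata.

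The Discussion raises selection as a possibility, in one direction: "widening access to surgery for higher-risk patients who would have been previously excluded, which might result in static or even worsened postoperative complication rates". Its answer is: "To account for this, we will also monitor changes in underlying patient characteristics, such as the percentage of patients in the most deprived quintile". Deprivation is chosen because it is a marker "which is strongly correlated with multimorbidity rates".

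**The concern.** Risk assessment and shared decision making can influence who goes on to an operation. If the risk profile of operated patients changes when the programme starts or is completed, the model assigns that change to its level and slope terms, that is, to the programme.

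This can work in two directions. Newly accepted higher-risk patients lower mean DAOH although care is no worse. Higher-risk patients who defer or choose no operation raise it although care after surgery is no better. The protocol recognises the first, which would look like harm or no effect. It does not recognise the second, which would look like benefit. Deferral is plausible for two of the three tracer procedures, since the protocol describes knee replacement as non-urgent and aneurysm repair as prophylactic.

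The Discussion presents monitoring as the way to account for the problem. Monitoring does not change the estimate, and nothing says how a movement in the monitored share would alter its interpretation. The one characteristic named is an area measure, whereas the risk at issue belongs to the individual patient.

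**Working it through.** The protocol gives no effect size, case-mix figure or prevalence by deprivation group, so there is no figure of its own to reproduce. Every numerical input below is an assumption except the lengths of the study periods.

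**1. How much of a risk shift the deprivation share shows**

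If the high-risk share of operated patients changes by dh, evenly across areas:
- change in most-deprived share = dh x (q_high - q_low), where q is the most-deprived share among high-risk or low-risk patients;
- change in mean DAOH30 = -dh x D, where D is the DAOH30 deficit of high-risk patients.

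Take 20% of patients in the most deprived fifth and multimorbidity of 50% overall.
- Multimorbidity 60% in that fifth, 47.5% elsewhere (0.2 x 60 + 0.8 x 47.5 = 50%): q_high = 0.2 x 0.6 / 0.5 = 24%; q_low = 0.2 x 0.4 / 0.5 = 16%. If multimorbidity rises from 50% to 60%, the share becomes 0.6 x 24 + 0.4 x 16 = 20.8%, a rise of 0.8 points.
- Multimorbidity 70% and 45%: q_high = 28%, q_low = 12%. The share becomes 0.6 x 28 + 0.4 x 12 = 21.6%, a rise of 1.6 points.

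With D of 1 to 3 days, mean DAOH30 falls by 0.10 x 1 = 0.1 to 0.10 x 3 = 0.3 days.

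Over a wider range (dh of 2 to 10 points, q_high - q_low of 3 to 20 points) the share moves by 0.06 to 2.0 points, or 3% to 20% of the risk shift.

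**2. The reverse direction**

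Suppose the 5% at highest risk have mean DAOH30 of 15 and the rest 26. If that 5% is no longer operated on, the mean changes from 0.95 x 26 + 0.05 x 15 = 25.45 to 26, a rise of 0.55 days.

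**3. What the segmented model does with pure selection**

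Simulation with no treatment effect: 62 baseline months (January 2018 to February 2023), 13 intervention months and 24 post-intervention months; ordinary least squares; 2,000 runs; independent monthly errors. The high-risk share moves 5 points from 20%, gradually over the intervention period. D = 4 days, SD = 6 days, q_high - q_low = 10 points. Each period indicator equals 1 only in its own period, so beta4 is the post-intervention level change from the baseline trend.

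| Operations per month (assumed) | beta4 for DAOH30 | Runs with beta4 significant | Runs with deprivation step (about 0.5 points) significant |
|---|---|---|---|
| 300 | about -/+0.20 days | 19-20% | 7% |
| 2,000 | about -/+0.20 days | 80-81% | 20% |
| 8,000 | about -/+0.20 days | about 100% | 61-63% |

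beta4 is negative when the high-risk share rises and positive when it falls. With D = 2 days the detection rates for DAOH30 and deprivation are 29-31% against 17-21% at 2,000 operations a month, and 81-82% against 58-60% at 8,000.

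**4. Whether the larger deprivation steps would be seen**

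In the same design with binomial noise only, a 0.8-point step is detected in about 10%, 40% and a little over 90% of runs at 300, 2,000 and 8,000 operations a month. For a 1.6-point step the figures are about 26%, a little over 90% and about 100%.

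**The case against.** Several points on the other side stand.

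- **Deprivation is an example.** The Discussion speaks of patient characteristics in the plural and introduces the deprivation share as one of them. A reader might infer that it is the only safeguard, or that the study would declare patient mix stable. The text says neither.
- **Age is already covered in part.** Trends within the four planned age groups would expose much of an age-driven change. They would not show a comorbidity change within an age or deprivation group.
- **Deprivation does carry information.** The Introduction says multimorbidity is commoner in deprived areas, and the Discussion calls the correlation strong. A reader might infer from step 1 that the share hardly moves. The documents give no figures for this, the even spread across areas is assumed, and step 4 shows that such a step can be visible at large volumes. Visibility still would not show how much of a DAOH change is due to case mix.
- **Selection is possible, not established.** The protocol says it may occur. Deferred patients may be optimised and operated on later, and a patient who declines surgery after discussion may be better off for it.
- **Some detail may lie elsewhere.** The supplementary list of data fields and any analysis plan are not shown, so the absence of a comorbidity definition is not itself the finding. The finding is that the article names the problem and offers a remedy that cannot account for it.

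**Conclusion.** The point holds in a limited form. The programme can change who is operated on, in either direction. All HES outcomes are conditional on surgery, the stated model has no case-mix term, and monitoring does not correct the estimate. The strata reveal part of a change in mix but not comorbidity within strata.

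The size is conditional on assumptions. A shift of 5 to 10 points in the high-risk share, with deficits of 1 to 4 days, gives a spurious DAOH30 change between 0.05 x 2 = 0.1 and 0.10 x 3 = 0.3 days across the cases worked above, including 0.05 x 4 = 0.2 days in the simulation. The most-deprived share would show a fraction of that risk shift.

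The documents do not support the stronger conclusions that selection will occur or that the deprivation share is uninformative. This should be changed, because without it a moderate rise or fall in the primary outcome is hard to interpret.

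**What to change.** In the Effectiveness statistical analysis section and the Discussion:

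1. Acknowledge both directions of selection, and replace the statement that monitoring accounts for it.
2. Define a comorbidity count from HES diagnoses in a fixed look-back before the index admission. The protocol describes HES thus: "It includes detailed information on hospital activities including admission dates, diagnoses and procedures, duration of stay and patient demographic information". Earlier diagnoses are preferable because screening may itself deepen coding at the index admission.
3. Fit the same segmented regression to the monthly number of operations for each tracer procedure, and to mean age and mean comorbidity count.
4. Prespecify DAOH30 standardised to the baseline age-comorbidity distribution as a sensitivity analysis beside the crude series, and read a difference between the two as possible case-mix change. Agreement should not be a condition for attributing an effect, since better patient selection may be one way in which the programme works.

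The cost is extra analysis and possibly a longer look-back in the data extract. The timeline puts the HES application and revision of the analysis plan in months 0 to 9, so both can still be arranged. The limitation is that patients without earlier admissions will have incomplete comorbidity information, which should be stated.
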